## Abstract

**Background:**

Extended liver resections still bear the risk of severe haemorrhage. Moreover, the amount of blood loss during liver resection determines the need for perioperative blood transfusions and is of prognostic relevance in oncologic surgery. Even though there is an ongoing debate about its effectiveness and tolerable duration, the Pringle Maneuver (PM) as an occlusion of the hepatic inflow is routinely applied to reduce blood loss during parenchymal dissection. In combination with the stapler resection technique, PM is expected to minimize blood loss during major liver resection safely due to the short parenchymal dissection duration.

**Methods:**

In a single center prospective, randomized, controlled, parallel, confirmatory trial the combination of PM and stapler resection technique in patients undergoing right and left hepatectomies will be tested against the control group that applies stapler resection without the use of PM. The primary endpoint of the study is the total intraoperative blood loss. The measurement of the intraoperative blood loss is conducted with respect to all handled rinse fluids during surgery and by weighing used swabs to generate accurate and comparable data. Secondary endpoints include intra- and postoperative blood transfusion requirements, liver function parameters and the 90-day mortality rate. A sample size of fifty-three patients in either group was calculated to detect a clinically significant difference in blood loss of at least 450 ml with an α of 5% at 80% power. The individual follow-up will be 90 days.

**Discussion:**

This is the first clinical trial to test the combination of PM and stapler resection technique as a means to reduce intraoperative blood loss in hepatic left or right resection. Given the short parenchymal dissection duration in stapler resection, PM is expected to be applied shortly without compromising liver function postoperatively.

**Trial registration:**

The PriMaL StHep trial has been prospectively registered to the German Clinical Trial Registry (WHO ID: DRKS00010427) on April 21st. 2016.

## Background

Resection is the standard treatment for a variety of benign and malignant pathologies of the liver. Depending on the size of the finding and the nature of the disease, resections can be performed as atypical or anatomical resections. Major liver resections, including left and right hepatectomies and their extensions listed in the Brisbane 2000 terminology [1], still carry the risk of severe hemorrhage [2]. Perioperative blood loss (BL) not only affects short-term outcome after surgery, it has been shown that extensive blood loss and transfusion of blood products are related to increased tumor recurrence in Hepatocellular Carcinoma (HCC) patients [3–6]. Voogt, et al. reported the same finding in colorectal cancer patients [7]. Accordingly, perioperative blood transfusions in colorectal metastases resection were found to be associated with impaired perioperative outcome, increased recurrence rate, and reduced long term survival [8, 9]. Currently, it was shown that a reduction of blood loss of 400 ml was associated with the absence of blood transfusions in a series of 186 liver resections [10]. Limiting intraoperative BL to avoid related blood transfusion therefore remains mandatory in liver surgery for malignancies; measures include resection along anatomical planes, maintenance of low central venous pressure (CVP), and blood saving resection techniques. Due to the varying application of these measures and the presence of other potential confounders, such as selection and reporting bias and uncontrolled circumstantial effects, case series and uncontrolled studies can only reveal limited understanding of strategies to successfully reduce the blood loss in major liver resections. Therefore, this single center Randomized Controlled Trial (RCT) which applies a highly standardized surgical technique that is limited to the clearly defined surgical procedure of left or right hepatectomy, was designed to evaluate this matter.

Conventional resection methods such as the Finger Fracture and the Clamp Crush techniques are challenged by the use of several innovative parenchymal dissection devices. Interestingly, a Cochrane database review of innovative and conventional liver resection techniques from 2009 revealed the traditional Clamp Crush technique to provide comparable or lower BL at lowest cost [11]. Traditionally, different modes of vascular occlusion are applied to further limit blood loss in liver resection. Total Hepatic Vascular Exclusion (THVE) includes the temporary ligation or clamping of the portal triad with simultaneous occlusion of the hepatic veins to prevent retrograde hemorrhage during resection, whereas the classic Pringle Maneuver (PM) only applies occlusion of the arterial and portal inflow. Due to the relative ischemia tolerance of the liver, Intermittent Pringle Maneuver (IPM) is utilized to facilitate extended resections with limited BL. There is little evidence from well-designed clinical trials to justify the widespread use of these techniques. A meta-analysis from 2008 revealed no advantage for the use of portal triad clamping in terms of perioperative outcome [12]. Additionally, the innovation of surgical techniques has led to a reduction in intraoperative BL, making inflow control dispensable. Through the use of vascular staplers, the duration of parenchymal resection has been significantly reduced to less than ten minutes for major hepatic resections with excellent safety [13, 14]. Nevertheless, a relevant blood loss still occurs, even in anatomic resections. This might be attributed to bleeding from the hepatic venous system, uncontrolled portoportal contralateral collaterals and failing to follow the precise anatomical segemental border during parenchyma dissection. Combining vascular occlusion techniques and stapler resection could help to further minimize intraoperative BL. It is assumed that the short duration of portal triad clamping has no negative impact on the perioperative outcome when applied in stapler hepatectomy. Therefore, this RCT was designed to evaluate the potential reduction of BL by the combination of stapler hepatectomy and PM.

### Objective

The trial’s objective is to test if PM reduces the intraoperative BL during left or right stapler hepatectomy. Furthermore, perioperative outcome is analyzed to evaluate the safety of the combination of PM and stapler resection technique.

### Hypotheses

Null hypothesis: The intraoperative BL in both groups does not differ to a clinically relevant extent with (H0): BL 1 = BL 2.

Alternative hypothesis: The intraoperative BL in both groups differs to a clinically relevant extent with (H1): BL 1 ≠ BL 2.

### Formal trial design

Single center prospective, randomized, controlled, parallel, open, confirmatory trial.

### Primary endpoint

Total intraoperative BL during stapler hepatectomy

Definition and assessment: The entire BL from skin incision to skin closure is defined as “intraoperative BL”. For the assessment of the exact amount of hemorrhage the volume of fluid in the suction container(s) that were used during the procedure are recorded in the case report form (CRF) by the end of the skin closure. Furthermore the numbers of all small and big surgical swabs are recorded. All swabs together with the container that catches dripping excess fluids underneath are weighed by the end of skin closure and the exact weight in grams is recorded in the CRF. The exact amount of rinse fluid in milliliters that was used during the procedure is recorded in the CRF.

The calculation of total BL is as follows: The suction container fluid volume (in milliliters) is added to the weight (in grams) of all surgical swabs and the drip catching container at the end of the skin closure (A). The amount of ascites that may be suctioned from the abdominal cavity initially is subtracted from that volume. The difference of the density of the rinse solution (isotonic sodium chloride solution) and blood is approximately 0.055 g/cm^3^. With regard to the exactness of the measurements this difference is considered clinically irrelevant.

The volume of the entire rinse fluid (in milliliters) that was used during the procedure is added to the known dry weight (in grams) of the respective number of surgical swabs that were used during the procedure and the known weight of the empty container they are weighed in (B).

The total BL is defined as “A” minus “B” in milliliters.

### Secondary endpoints

Intraoperative BL per resection plane size (ml/cm^2^)Number of packed red blood cells (PRBC) transfused intraoperativelyPostoperative ALT levels day 1 and 3 (and their relative delta)Postoperative total bilirubin levels day 1 and 3 (and their relative delta)Postoperative INR day 1 and 3 (and its relative delta)Number of PRBC transfused within the first three postoperative daysGeneral surgical complications, classified according to the “Clavien – Dindo” classification within the first 30 postoperative daysMortality during the first ninety postoperative days

### Tested method

All procedures are performed according to institutional standards for liver surgery. Depending on the planned procedure, an upper midline incision with or without right lateral extension (“reversed L – shape”) is performed in a regular dorsal position. After the hepatic lesion is confirmed to be treatable by resection, the liver is freed from its ligaments and mobilized. In the treatment group Classic PM is performed via silicon tube tourniquet of the portal triad just before the resection starts. If the parenchymal resection exceeds fifteen minutes, the tourniquet will be loosened for five minutes followed by intermittent PM with five minute intervals of ischemia and reperfusion until the parenchymal resection is finished. Liver resection itself is performed in the stapler technique as described elsewhere [14]. Briefly, after identification of the resection plane, demarcation of the resection line by ligation of the specific hepatic arterial and hepatic vein branches, the parenchyma is stepwise fractured with a straight vascular clamp and dissected with an Endo GIA vascular stapler (Medtronic, Endo GIA™ Universal Roticulator 60–2.5 or Endo GIA™ Curved Tip 60 mm Articulating Vascular/Medium Tri-Staple™) in an alternating manner. After removal of the resected specimen, pressure with a hot, wet surgical swab is applied to the resection plane and PM is terminated immediately thereafter by loosening of the tourniquet. In all cases the central venous pressure will be kept at 5 mmHg or below by the anaesthesiologists according to routine liver surgery standards in our institution.

### Risks of the tested method

Liver resection naturally carries the risk of bleeding, independent of the resection technique used. After PM was first described as a means of haemorrhage control in liver trauma [15], it has been applied by liver surgeons to limit blood loss during elective liver resections. Potential harmful effects of PM have been widely discussed over decades. Based on the work of Huguet from 1994 it is widely accepted that warm ischemia due to PM is tolerated by healthy, non-cirrhotic livers for up to sixty minutes [16]. The parenchymal damage caused by ischemia reperfusion is commonly monitored by measurement of perioperative Liver transaminase levels. A meta-analysis on the use of PM in 2008 showed no statistical difference in Transaminase levels when PM was compared to hepatic resection without vascular occlusion [12]. Liver cirrhosis is prevalent in many cases of hepatic resections, especially for HCC. Based on experimental [17] and clinical [18–20] data, cirrhotic livers are more sensitive to ischemic damages including inflow occlusion. This effect is believed to be strongly dependent on the duration of the ischemic period. Accordingly, a clinical trial from 2004 found an advantage for intermittent portal clamping compared to continuous clamping in cirrhotic patients [21]. In this trial short ischemic periods of five minutes, followed by five minutes of reperfusion repetitively, were found to decrease the ischemia reperfusion damage in cirrhotic livers indicated by blood tests.

PM has been proven to be applied safely for up to sixty minutes in non-cirrhotic livers. By intermittent inflow occlusion the duration of resections under ischemia could be extended to up to 120 min [22]. To prevent potential harm in single cases with prolonged duration of parenchymal resection, after fifteen minutes the tourniquet will be loosened for five minutes. In the following intermittent PM with five-minute intervals of ischemia and reperfusion will be applied until the parenchymal resection is finished. Considering the average duration of parenchymal resection in this trial to be less than ten minutes in total, no harmful effects are expected to be caused by PM in the treatment group.

### Inclusion criteria

Patients undergoing open left or right hepatectomy according to the Brisbane classification for benign or malignant diseases)Age of eighteen years or olderWritten informed consent for participation in the trialAbsence of a mental state preventing the subject to understand the study related information

### Exclusion criteria

Situation post interventional or operative portal vein embolization or ligationAnatomical alterations which render study treatment impossible (e.g. a biliodigestive anastomosis, an extraanatomic hepatic artery bypass, and/or any other circumstance which renders PM or stapler resection impossible)Simultaneous resection of other organs (excluding the gall bladder and the common bile duct)Liver cirrhosis exceeding Child – Pugh score A

### Patient selection

All patients who are scheduled for open left or right hepatectomies are screened for participation in the trial by a member of the Clinical Trial Center (KSC) of the Department of Surgery, University Hospital Heidelberg. Written informed consent is obtained from every subject on the day before surgery the latest. Due to expected drop outs because of intraoperative exclusion of screened patients, approximately 155 patients will be screened to include 106 patients in the final analysis. Figure 1 gives an overview of the patients' course through the trial. According to the above-mentioned inclusion and exclusion criteria subjects are randomized equally to either of the two groups intraoperatively:Controls – liver resection applying standard stapler parenchymal resection technique without hepatic inflow control as described previously [14]Treatment group – liver resection applying standard stapler parenchymal resection technique with continuous PM (intermittent PM after fifteen minutes of parenchymal resection)

**Fig. 1 Fig1:**
[figure not shown]
Trial Flowchart according to CONSORT

### Randomization

#### Randomization process

The randomization will facilitate numbered, opaque envelopes, derived from a computer-generated random list by a member of our institution who is not involved in the trial otherwise. After the surgeon has performed the laparotomy and verified that the resection can be performed as planned without any impediments to the trial treatments, the KSC will be informed. The allocation to the treatment or control group in a 1:1 ratio will be done by a member of the KSC by opening the respective envelope and immediate informing of the operating team about the result. The result of the randomization will be recorded in the CRF. The stratification used for randomization is the type of resection: left / right hepatectomy.

### Trial duration

Based on the sample size calculation (2.4.1), the evaluation of the last patient will be completed (last patient out) 31 months after the start of screening for eligible patients (first patient in). Another three months later the results of the data analysis will be available. The individual duration of the trial for each patient is 91 days (randomization on the day of surgery, follow up 90 days postoperatively). Table 2 gives an overview of the trial schedule according to the SPIRIT statement [25].

**Table 2 Tab2:** Trial visits schedule

Trial visits					
Trial activity/examination	Preoperatively	Day of surgery	POD 1 and 3	POD 30	POD 90
Screening, informed consent, preoperative baseline data (Table 1)	X				
Type of resection (left/right hepatectomy)/BL/resection plane surface in cm^2^/number of transfused PRBC/duration of parenchymal resection/duration of PM/central venous pressure during resection/time from skin incision to completion of skin closure/protocol violations		X			
ALT/AST/total bilirubin/GGT/AP/INR/total albumin/numbers of transfused PRBCs/incidence of wound healing disorders/incidence and type of biliary leakage			X		
Incidence and type of wound healing disorders/incidence and type of biliary leakage/duration of hospital stay/mortality				X	
AE/SAE		X	X	X	
Mortality					X

*POD* Postoperative day, *BL* blood loss, *PRBC* packed red blood cells, *PM* Pringle Maneuver, *ALT* alanine aminotransferase, *INR* international normalized ratio, *AE* adverse event, *SAE* serious adverse event

### Termination of the trial

#### Individual criteria

If a patient withdraws his consent to participate in the trial, no further data collection is done and all of his data will be deleted upon demand. The patient will be asked for the allowance to analyse the data that was collected before the withdrawal of consent.

#### Termination of the entire trial

If new findings during the course of the trial reveal any safety concerns regarding the investigated method, all trial activity will be interrupted. If substantial safety concerns remain, the entire trial will be terminated.

Scheduled termination of the trial is when at least 53 patients in both trial arms have completed the follow up.

### Sample size

In our institution major liver resections are commonly performed without PM. Based on the intraoperative course, e.g. if extensive BL during parenchymal resection occurs, PM is performed according to the surgeon’s appraisal. In a retrospective analysis of 193 major liver resections that were performed in our institution from January 2011 until February 2014, we found a reduction of the mean intraoperative BL of 27.4% (647 (+/− 612) vs. 891 (+/− 783) ml) in the 62 cases with PM. Since PM was only used when an extensive, uncommon BL was detected, we expect the effect of PM to be substantially higher among standard major liver resections in general. Even though it is a generally accepted fact that blood loss and PRBC transfusions during liver surgery negatively affect patients’ outcome, it is uncertain if the effect is straight proportional. In a recent work Wehry et al. showed that the average amount of blood loss in 186 patients undergoing liver resection was reduced by approximately 400 ml if transfusions were not required [10]. In this context it appears reasonable that this interventional trial should be designed powerful enough to detect a reduction of blood loss of at least 400 ml. The sample size calculation for this trial is therefore based on the assumption that a reduction of the intraoperative BL has to be at least 50% (a reduction of approximately 450 ml) to be clinically relevant. Therefore, 53 patients have to be analyzed in each group to detect a 50% reduction of BL at a standard deviation of 94.1%, an alpha of 5% and an 80% power level. Assuming a realistic dropout rate due to intraoperative findings, contraindications for major liver resection and other reasons 155 patients are planned to be screened and asked for participation in the trial.

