### Statistical methods

The non-parametric Mann-Whitney u test will be used to compare the intraoperative BL values between both treatment groups.

The Fisher’s exact test will be performed to compare the rates of 30-day mortality, bile leakage, intraoperative transfusion requirements, and blood transfusion requirements within the first three postoperative days between both treatment groups.

Depending on the distribution of the quantitative parameters intraoperative BL per resection plane size, duration of surgical procedure, and duration of hospital stay the T-test in case of a normal distributed parameter or the non-parametric Mann-Whitney-U-Test will be used to compare both treatment groups.

The postoperative ALT levels, total bilirubin levels, and INR at day 1 and at day 3 will be compared between both treatment groups using the T-test or the Mann-Whitney-U-Test. The Bonferroni-Holm method will be used to adjust the *p*-values.

Two-sided p-values < 0.05 will be considered as statistically significant.

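### The printed sample-size inputs give 56 to 60 patients per group rather than 53, and the section names both 400 ml and about 450 ml as the difference to detect

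*Protocol article*

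**What the plan says.** All places are in the protocol article.

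- **Sample size, target.** Citing a series of 186 liver resections, the section says that the trial "should be designed powerful enough to detect a reduction of blood loss of at least 400 ml".
- **Sample size, calculation.** The next sentence bases the calculation on a 50% reduction, glossed as "a reduction of approximately 450 ml". The result is that "53 patients have to be analyzed in each group to detect a 50% reduction of BL at a standard deviation of 94.1" per cent, with "an alpha of 5% and an 80% power level".
- **Sample size, cohort.** The institution's 193 retrospective major resections had mean blood loss of 647 ml (SD 612) in the 62 cases with the Pringle maneuver and 891 ml (SD 783) in the others.
- **Abstract, Methods.** The same 53 per group is said "to detect a clinically significant difference in blood loss of at least 450 ml".
- **Statistical methods.** For the primary endpoint, "The non-parametric Mann-Whitney u test will be used to compare the intraoperative BL values between both treatment groups". The significance rule is "Two-sided p-values < 0.05 will be considered as statistically significant".
- **Randomization.** Allocation is 1:1.

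**The concern.** Everything needed to recompute the sample size is printed, and the printed answer does not come out. The 94.1% has no stated base, and neither mean-SD pair shown beside it produces it.

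The reasoning from 400 ml to 450 ml also runs the wrong way. A design with 80% power for a larger difference has less than 80% for a smaller one at the same SD, so sizing for 450 ml does not secure a 400 ml target.

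What is at stake is how a result is read. The trial is described as confirmatory. A non-significant result would be judged against 80% power for a difference that is 400 ml in one sentence and about 450 ml in the next, with an SD that does not quite give 80%. Type I error and the treatment estimate are not affected.

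**Working it through.** **Inputs.** Reduction 50%, SD 94.1%, alpha 5%, power 80% (Sample size); two-sided, Mann-Whitney (Statistical methods); 1:1 (Randomization). The 53 is already the number analysed, so no dropout allowance enters it.

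**1. Attempt to reproduce 53.**

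n per group = 2 × (1.960 + 0.842)² × (SD/difference)² = 2 × 7.849 × (94.1/50)² = 15.70 × 3.542 = 55.6, so **56**.

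- Exact t-test: 56.6, so **57**.
- Mann-Whitney with normal data (relative efficiency 3/π = 0.955): 55.6/0.955 = 58.2 and 56.6/0.955 = 59.2, so **59 to 60**. Noether's formula gives 61.
- Other readings: one-sided 44 to 45; SD proportional to each group's mean 35; log scale 21; Mann-Whitney with a logistic parent 52; 450 ml with an SD of 838 ml 55.

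None gives 53. At 80% power, 53 would need an SD of about 91.9% or a reduction of about 51.2%.

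**2. Power of 53 per group on the printed inputs.**

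Normal approximation: (50/94.1) × √(53/2) − 1.960 = 0.531 × 5.148 − 1.960 = 0.775, which gives 78.1%. The t-test gives 77.3%. Mann-Whitney with normal data gives 76.2% by the efficiency factor and 76.4% by simulation (4,000 runs).

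**3. Origin of 94.1%.** 612/647 = 94.6% and 783/891 = 87.9%. Neither matches.

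**4. Power at 400 ml.** Half of 891 ml is 445.5 ml, close to the stated 450 ml, so the percentages appear to refer to a base of about 891 ml. This is an inference. On that base the SD is 0.941 × 891 = 838 ml. Because the base is not stated, the SD is varied. The pooled cohort SD, with 193 − 62 = 131 cases without the maneuver, is √[(61 × 612² + 130 × 783²)/191] = 733 ml.

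Power with 53 per group, as normal approximation / t-test / Mann-Whitney with normal data (efficiency factor):

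| SD (ml) | Source | At 400 ml | At 450 ml |
|---|---|---|---|
| 838 | 94.1% of 891 | 69 / 68 / 67% | 79 / 78 / 77% |
| 783 | cohort, no maneuver | 75 / 74 / 73% | 84 / 83 / 82% |
| 733 | cohort, pooled | 80 / 80 / 78% | 89 / 88 / 87% |
| 703 | √[(612² + 783²)/2] | 83 / 83 / 82% | 91 / 90 / 90% |

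At 838 ml, 80% power for 400 ml would need 69 per group (normal approximation) or 70 (t-test). Simulated Mann-Whitney power at 838 ml and 400 ml is 66%.

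**5. Skewed data.** With a proportional reduction and a constant coefficient of variation of 0.941, simulated Mann-Whitney power with 53 per group is 80% (gamma) to 97% (lognormal) at 400 ml, and 91% to 99% at 445.5 ml.

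**The case against.** **The design may be adequate for 400 ml.** A reader might infer from the printed SD that the trial lacks 80% power at 400 ml. The document does not establish that. With the pooled cohort SD the normal formula gives 2 × 7.849 × (733/400)² = 52.7, so 53 per group: the section's own target and its own cohort reproduce its sample size. The normal model is also a poor one for blood loss. With an SD of 838 ml it puts about 14% of controls (mean 891 ml) and about 30% of treated patients (mean about 445 ml) below zero. Under the skewed models tried, power at 400 ml reaches 80% or more. This stands, so the shortfall can only be stated conditionally. It does not rescue the text, because the protocol states neither that SD nor any distribution.

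**The 94.1% may have a sound source.** The section does not say that it is a ratio of the printed summaries. The cohort covers major resections while the trial takes only open left or right hepatectomies, and the full protocol is not shown. This also stands: the figure cannot be called impossible, only unmatched and without a stated base.

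**A misprint.** A reader might infer that 94.1 is 91.4 with digits transposed, since 703 ml over the midpoint of the two means, 769 ml, is 91.4%. Nothing in the document supports this. It would make 50% equal to about 385 ml, against the stated 450 ml or so, and the pooled-SD route reaches 53 without any misprint.

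**The miss is small.** It is 3 to 4 per group by the normal formula or t-test and 2 to 3 points of power. The termination rule treats 53 per arm as a minimum, and the abstract agrees with the calculation on 450 ml. All of this stands and bears on severity.

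**Conclusion.** The paragraph is wrong as written, by a small amount. The printed inputs require 56, 57 or 59 to 60 per group depending on the method, and 53 gives about 76% to 78% power instead of 80%. The normal-formula and t-test results need only two-sided testing and equal allocation, both stated. The Mann-Whitney result also assumes normal data.

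The two target differences are inconsistent. How much power 400 ml has is open: about 67% to 69% if the SD is 838 ml, about 80% if it is 733 ml, and possibly more with skewed data. The 838 ml reading rests on the inferred base of 891 ml.

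This is a minor correction to the stated basis of the primary comparison. It does not show that the trial is underpowered or that more patients are needed.

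**What to change.** Keep 53 per group. In the Sample size section and the abstract:

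1. Name one target difference in ml, and one SD in ml with its source and base.
2. Correct either the 94.1% or the stated 80% so that both agree with 53, and name the formula.
3. Give power for the Mann-Whitney test under a stated distribution at both 400 and 450 ml. The normal-data figures on the 838 ml SD should not stand as the only ones.
4. Keep the 400 ml statement only if the corrected SD supports it.

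The SD should come from the planning record or pre-trial data, not from the trial's own results. The cost is a reworded paragraph and one abstract sentence, with no extra patients and no change to the analysis. The stated power may turn out somewhat lower or higher than 80%.
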